## Abstract

The MASS III Trial is a large project from a single institution, The Heart Institute of the University of Sao Paulo, Brazil (InCor), enrolling patients with coronary artery disease and preserved ventricular function. The aim of the MASS III Trial is to compare medical effectiveness, cerebral injury, quality of life, and the cost-effectiveness of coronary surgery with and without of cardiopulmonary bypass in patients with multivessel coronary disease referred for both strategies. The primary endpoint should be a composite of cardiovascular mortality, cerebrovascular accident, nonfatal myocardial infarction, and refractory angina requiring revascularization. The secondary end points in this trial include noncardiac mortality, presence and severity of angina, quality of life based on the SF-36 Questionnaire, and cost-effectiveness at discharge and at 5-year follow-up. In this scenario, we will analyze the cost of the initial procedure, hospital length of stay, resource utilization, repeat hospitalization, and repeat revascularization events during the follow-up. Exercise capacity will be assessed at 6-months, 12-months, and the end of follow-up. A neurocognitive evaluation will be assessed in a subset of subjects using the Brain Resource Center computerized neurocognitive battery. Furthermore, magnetic resonance imaging will be made to detect any cerebral injury before and after procedures in patients who undergo coronary artery surgery with and without cardiopulmonary bypass.

Clinical Trial registration information

ISRCTN59539154 Off-pump vs. on-pump surgery in patients with Stable CAD MASS III

## Introduction

Coronary bypass surgery performed without the use of cardiopulmonary bypass (off-pump surgery) has been used sporadically since the beginning of the bypass surgery era in 1967, but the use of this strategy increased substantially during the 1990s. The major reason for the increased use of off-pump surgery was the hope that this strategy would decrease perioperative morbidity and possibly mortality by eliminating cardiopulmonary bypass (on-pump surgery). The fear concerning off-pump surgery has been that the difficulty of operating with the heart beating would lead to less-complete and less-effective revascularization at the time of surgery and worse long-term outcomes. These advantages and disadvantages have been examined in several studies that compared the outcomes of patients undergoing off-pump and on-pump surgery [1-4]. Observational trials often have shown bigger differences in short-term complications, usually in favor of off-pump surgery, but analyses of these trials are complicated by patient selection. On the other hand, randomized trials usually have shown small differences in perioperative outcomes, usually slightly in favor of off-pump surgery, mostly including low-risk patients.

Long-term follow-up studies, both randomized and observational, have sometimes noted inferior outcomes after off-pump compared with on-pump surgery, manifested as decreased patency, increased risk of repeat revascularization, or increased mortality. Yet, other studies have shown no or few long-term differences that usually have been attributed to a lack of experience with off-pump surgery [3,4].

The absence of guidelines for the use of one or the other technique has allowed individual decision-making according to the experience of the surgeon [5]. The rationality for off-pump surgery is reduced morbidity, and reduced adverse effects attributed to on-pump surgery, including an inflammatory response caused by the circulation of blood through the cardiopulmonary circuit and the formation of microemboli [6]. In this context, the advantages and disadvantages of both strategies have been considered, and critical appraisal is made of the evidence available. The validity of evidence has been assessed using different criteria, including study design, size of surgical populations, and the quality of statistical analyses [7].

### Objectives

The aim of the MASS III Trial is to compare medical effectiveness, safety, cerebral injury, quality of life, cost-effectiveness of coronary surgery with and without of cardiopulmonary bypass in on-pump and off-pump techniques in patients referred for both strategies. The primary endpoint should be a composite of cardiovascular mortality, cerebrovascular accident, nonfatal myocardial infarction, and refractory angina requiring revascularization.

### Rationale

Coronary artery surgery with and without cardiopulmonary bypass plays an important role in the treatment and management of ischemic heart disease. Both treatment strategies have their own advantages and disadvantages. On-pump strategies provide more complete revascularization and require fewer repeat interventions compared with off-pump surgery. However, the procedure is more invasive and is associated with cardiac as well as noncardiac surgery morbidity [8,9]. Major neurological complications after conventional cardiac surgery have been reported to occur in 3.1% of patients [10]. Additionally, neuropsychological dysfunction is increasingly being recognized as a complication of on-pump surgery. Cognitive deficits can be documented accurately [11] and may occur in up to 38% of patients [12]. The increasing awareness of the cerebral complications following on-pump surgery especially in the elderly [13] has led to a renewed interest in coronary surgery on the beating heart. The Utrecht Octopus method is a technique developed to avoid cardiopulmonary bypass and the complications associated with its use [14].

The role of off-pump surgery, however, is the subject of debate. Opponents emphasize the excellent results of conventional on-pump surgery and express their concerns about the safety, early anastomotic failure, and eventual incomplete revascularization related to off-pump strategies [15].

Moreover, although widely accepted, the suspected deleterious role of cardiopulmonary circulation in the genesis of adverse cerebral outcomes has not been completely proved, simply because an appropriate control group has never been available. A limited number of randomized clinical trials have directly compared coronary surgery with and without cardiopulmonary bypass circulation [16,17].

## Methods

The MASS III trial is a single-center, prospective, randomized clinical trial, of which the design, timing of investigation and definitions of main outcome events are presented in Figure 1, Table 1 and Table 2, respectively. The MASS III Trial provided external blinded committee. So, all nonfatal clinical events, including MI, Stroke, refractory angina requiring revascularization, will undergo central adjudication by independent Clinical Events Committee (CEC). The role of CEC will be to insure that all primary endpoint are adjudicated uniformly. Furthermore a cardiopulmonary surgeon, a cardiologist and a neurologist formed the clinical event committee and confirm and classify the major adverse cardiac and cerebrovascular events (MACCE), blinded to the treatment. To verify whether important differences in the incidence of MACCE exist between the treatment groups, the Data Monitoring Committee performed an interim analysis after the first patients 100 had entered each arm of study. The three members of this committee are experienced in patient-oriented research, are independent of the study, and may also offer unsolicited recommendations. The sample size calculations are based on the assumptions that the actuarial freedom from cardiac event rate 5 years after on-pump surgery is 95% and that off-pump surgery did not decrease the rate by more than 10%. The α error is set at 0.05, and the β error is set at 0.20. The required sample size is 153 in each group for a total of 306 patients.

**Figure 1 F1:**
[figure not shown]
**Algorithm MASS IIItrial.** Only patients eligible for off-pump can enter the study. *Crossing-over in presence of electric or hemodynamic instability.

**Table 1 T1:** Schedule of Measurements

	S	P	D	1 m	3 m	6 m	12 m	24 m	36 m	48 m	60 m
Angiograms	X		X								X
History/events	X	X	X	X	X	X	X	X	X	X	X
Anginal assessment	X	X	X	X	X	X	X	X	X	X	X
Medications	X	X	X	X	X	X	X	X	X	X	X
Physical examination	X	X	X	X	X	X	X	X	X	X	X
Electrocardiography	X	X	X	X	X	X	X	X	X	X	X
Echocardiography	X										X
Magnetic Resonance Imaging	X		X								
Neuropsychological tests	X		X		X	X					
Routine laboratory	X	X	X	X	X	X	X	X	X	X	X
ECG stress tests	X					X					X
Resource utilization	X	X	X	X		X	X	X	X	X	X
Quality of life	X					X	X	X	X	X	X
Cost-effectiveness		X	X								
Working status	X				X						

Abbreviations: S = preprocedural screening; P = procedure; D = discharge; 1 m = 1 month after intervention; 3 m to 60 m denotes months after intervention.

**Table 2 T2:** Definitions of Main Composite Primary End Points

**Cardiovascular death**	Cardiovascular mortality is included in the composite primary end point. Cardiovascular death includes fatal myocardial infarction, sudden death, untreated heart failure, fatal cerebral infarction, and hemorrhage and procedure-related fatal bleeding.

**Cerebrovascular accident**	Patients with a focal neurological deficit of central origin lasting more than 72 hours, or a focal neurological deficit of central origin lasting more than 24 hours with imaging evidence of cerebral infarction or intracerebral hemorrhage, or a nonfocal encephalopathy lasting more than 24 hours with imaging evidence of cerebral infarction or hemorrhage adequate to account for the clinical state. Retinal arterial ischemia or hemorrhage is also included. To fulfill the definitions of stroke, the deficit must be new, sudden in conset, and not attributable to any more likely alternative cause.

**Myocardial infarction**	Elevation of specific cardiac enzymes within 14 days of a revascularization procedure and presence of new Q waves in at least 2 or more contiguous leads and CK-MB elevation 5 × normal (see Appendix).

**Further revascularization**	The initial revascularization is considered completed when the patient is transferred from the operating room to bed. Refractory angina requiring revascularization was considered an end point.

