### Secondary End Points

The secondary end points in this trial include non-cardiac mortality, presence and severity of angina, quality of life using the SF-36 Questionnaire [18], and cost-effectiveness at discharge and at 5-year follow-up. In this scenario, we will analyze the cost of the initial procedure, hospital length of stay, resource utilization, repeat hospitalization, and repeat revascularization events during the follow-up. Exercise capacity will be assessed at 6-month, 12-month, and end follow-up.

In the MASS III trial, no difference is expected in cardiac outcome; nevertheless, cardiac death, myocardial infarction, and repeat revascularization procedures will be assessed in-hospital and at 1, 6, and 12 months and yearly thereafter. Cognitive function will also be assessed at baseline and at 1, 6, and 12 months. It is expected that most patients will show a decline in this early postoperative period. However, the rapid recovery and short hospital stay of the nonselected patients who undergo coronary surgery in our hospital without extracorporeal circulation suggest that the benefits of this strategy may be especially reflected in a reduction of neuropsychological injury in the early postoperative period.

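### Table 1 ties the only postoperative MRI and the first postoperative neuropsychological test to discharge, which treatment may affect, so the arms may be assessed at different postoperative times

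*Protocol article*

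**What the plan says.** The protocol article's Table 1 (Schedule of Measurements) defines its columns as "Abbreviations: S = preprocedural screening; P = procedure; D = discharge; 1 m = 1 month after intervention; 3 m to 60 m denotes months after intervention". After the procedure, every column except discharge is a fixed number of months.

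- The row "Magnetic Resonance Imaging" is marked at screening and discharge only. The Abstract gives the purpose: "magnetic resonance imaging will be made to detect any cerebral injury before and after procedures".
- The row "Neuropsychological tests" is marked at screening, discharge, 3 months and 6 months.
- Secondary End Points gives a different cognitive schedule, with no discharge test: "Cognitive function will also be assessed at baseline and at 1, 6, and 12 months".
- For clinical events, the same section says that "cardiac death, myocardial infarction, and repeat revascularization procedures will be assessed in-hospital and at 1, 6, and 12 months and yearly thereafter".
- Hospital length of stay is among the items to be analysed. As a reason to expect less early neuropsychological harm off-pump, the section cites "the rapid recovery and short hospital stay of the nonselected patients who undergo coronary surgery in our hospital without extracorporeal circulation".

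**The concern.** Discharge is not a fixed point on the postoperative clock. It happens after randomization, and the trial itself treats length of stay as something the surgical strategy might change. If one arm goes home sooner, its discharge MRI and discharge test are done on an earlier postoperative day. The protocol expects most patients to decline cognitively soon after surgery and expects any off-pump advantage to show mainly in that period. That is when a difference of a few days in test date can matter most.

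An early difference between arms could then reflect the operation, the day of measurement, or both. For the MRI there is no later scan at a common time to fall back on. A similar issue applies to in-hospital event counts, whose observation time ends at discharge and so may differ in length between arms.

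**Working it through.** The protocol gives no figure on this point to reproduce, and the sample size calculation does not enter. The check is mainly a comparison of the stated rules.

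**Step 1: which assessments depend on discharge.** From Table 1 and Secondary End Points:

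| Assessment | Tied to discharge | Postoperative fixed times |
|---|---|---|
| MRI (Table 1) | yes | none |
| Neuropsychological tests (Table 1) | yes | 3, 6 months |
| Cognitive function (Secondary End Points) | no | 1, 6, 12 months |
| Cardiac death, infarction, repeat revascularization (Secondary End Points) | in-hospital assessment | 1, 6, 12 months, then yearly |
| Clinical composite (Primary Composite End Points; Cox model) | no | time to event over 5 years |

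The MRI depends wholly on discharge. The early cognitive test does so only if Table 1 prevails over the text. The early event comparison has a fixed 1-month visit beside it.

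**Step 2: can discharge differ by arm?** Length of stay is analysed as an outcome, and a short off-pump stay is offered as a sign of that strategy's benefit. A systematic difference is therefore plausible on the trial's own reasoning. No number of days is given for either arm, and no on-pump comparator is stated.

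**Step 3: size.** It cannot be computed. The two illustrations below assume no true difference between arms. Everything in them is assumed except the two anchor rates, which are borrowed from the literature figures in the Rationale and are not trial estimates.

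(a) *Discharge cognitive test.* Suppose 38% of on-pump patients show a deficit at their test, deficits resolve with a half-life of h days, and off-pump patients are tested g days earlier. The off-pump reading is 0.38 × 2^(g/h).
- g = 1, h = 30: 0.38 × 2^(1/30) = 0.389, a spurious 0.9 points against off-pump.
- g = 3, h = 7: 0.38 × 2^(3/7) = 0.511, a spurious 13.1 points against off-pump.

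(b) *In-hospital events.* Suppose a 3.1% on-pump in-hospital rate, the same constant hazard in both arms, and an off-pump stay that is a fraction r of the on-pump stay. The off-pump reading is 1 − (1 − 0.031)^r.
- r = 0.9: 2.8%.
- r = 0.6: 1.9%.

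This favours off-pump, the opposite direction to (a). If events cluster close to surgery, cutting the last days off the window removes fewer events than a constant hazard implies, so (b) would overstate the effect.

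For the MRI, the article says nothing about how detection changes with postoperative day, so neither a direction nor a size can be given.

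**The case against.** The strongest counter-arguments, and what stands of each:

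- **The main results do not depend on discharge.** This stands. The clinical composite runs over 5 years under a Cox model. The cerebral end point is cumulative over 5 years and is not a separate in-hospital comparison. A deficit found at a discharge test could still enter it, if that test is kept and counted.
- **Early events are already covered.** This largely stands. Events are collected at 1 month, and the infarction definition in Table 2 uses a fixed 14-day limit after revascularization. Nothing makes an in-hospital rate the decisive comparison.
- **The cognitive tests may all be at fixed times.** This stands as a limit. Under Secondary End Points there is no discharge test and the problem does not arise for cognition. Even Table 1 adds tests at 3 and 6 months, and the battery is given only to a subset of patients.
- **A discharge column in an article is shorthand, with exact days left to the full protocol.** This stands only in part. The article does not merely omit a day; it states discharge as the time point, in a table whose later columns are all fixed.

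A reader might go further and infer that the arms are in fact measured at different postoperative ages, or that no early result can be attributed to bypass. The document does not support that. It describes the off-pump stay as short without comparing it with on-pump or giving days, so unequal timing is a likely consequence, not a documented fact.

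**Conclusion.** The point holds for the postoperative MRI, and for the early neuropsychological test if Table 1 is the schedule in force. Both are taken at a time that treatment may influence, so timing competes with bypass as an explanation for any early difference. The MRI is the clearest case, since it has no fixed-time repeat and does not depend on the conflict over cognitive visits. For clinical events the point is minor: it concerns only how in-hospital counts are used.

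No size can be stated. The illustrative ranges, 0.9 to 13.1 percentage points for a cognitive deficit rate and 2.8% to 1.9% against 3.1% for in-hospital events, rest on assumed gaps, recovery rates and hazards. They show only that the effect could be anything from trivial to material. The 5-year composite is unaffected. The change is worth making, but the trial's main comparison does not hang on it.

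**What to change.** 1. Reconcile Table 1 (discharge, 3 and 6 months) with Secondary End Points (1, 6 and 12 months) on cognitive testing, so that one schedule applies.
2. For the MRI and any early cognitive test that remains, replace the discharge column with one fixed postoperative day and a narrow window common to both arms, chosen within the usual stay where possible. Record the actual date.
3. For patients already assessed at discharge, report the test day by arm. Adjust for it only as a sensitivity analysis: test day at discharge is essentially length of stay, so adjustment conditions on a variable that treatment may affect and can itself introduce bias.
4. Make the early between-arm event comparison at 30 days after surgery for every patient, using the 1-month visit already scheduled. Keep in-hospital counts as descriptive only.

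The cost is a change of schedule wording, plus one return session for some patients discharged before the test day. The 30-day comparison needs no new visit.

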### Primary Composite End Points

The primary endpoint should be a composite of cardiovascular mortality, cerebrovascular accident, nonfatal myocardial infarction, and refractory angina requiring revascularization across 5 years of follow-up.

It is expected that the need for repeat revascularization after coronary surgery with or without cardiopulmonary bypass will be similar. As mentioned, a controversy discussed in the literature indicates that coronary surgery with or without cardiopulmonary bypass circulation has equal effectiveness in terms of myocardial revascularization. Therefore, repeat interventions can be a major clinical event. Therefore repeat interventions will be considered as early failure of treatment in this study. In addition, the use of cardiopulmonary bypass can be associated with considerable cerebral injury, in particular neuropsychological deficits [11,12]. So, the primary end point in the comparison of surgery with and without cardiopulmonary bypass is also a cerebral event. This is defined as the proportion of patients free of the combined event of fatal and nonfatal cardiovascular accidents and cognitive dysfunction, whichever occurs first, to be determined in-hospital and during the 5 years of follow-up.

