## Appendix: Definition of myocardial infarction

**A** – Q-Wave infarction

See ECG-criteria new Q-wave infarction

Enzyme elevation as follows:

CK-MB elevation 5 × upper limit of normal

**B** – Enzymatic/non-Q-wave infarction

Enzyme elevation as follows:

CK-MB elevation 5 × upper limit of normal

**C** – ECG Criteria New Q-Wave myocardial infarction

New QS in 2 associated leads in the absence of left bundle-branch block (LBBB)/Wolf-Parkinson White Syndrome.

New QS in 2 associated leads, defined as ≥ 0.04 seconds broad and/or Q/R ratio ≥ 1/4

Posterior wall infarction: new Broad R-wave (≥ 0.04 seconds) and tall R/wave (R/S ratio▶1 or R-wave ≥ 0.5 mv) in lead V1 and V2 in the absence of right bundle-branch block (RBBB)/right ventricular hypertrophy (RVH)

New permanent LBBB and enzyme elevation

Reversed R-wave progression precordial: decrement R-wave ≥ 0.2 mv in 2 consecutive precordial leads and enzyme elevation.

Any new Q-wave in lead V2 and V3 and enzyme elevation.

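### The protocol prints two incompatible definitions of myocardial infarction for its primary endpoint, and neither gives a rule for spontaneous infarction during the 5 years

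*Protocol article*

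**What the plan says.** The Methods section of the protocol article names Table 2 as the place where the main outcome events are defined. For MI, Table 2 requires "Elevation of specific cardiac enzymes within 14 days of a revascularization procedure and presence of new Q waves" and continues "in at least 2 or more contiguous leads and CK-MB elevation 5 × normal (see Appendix". The enzyme window, the Q waves and the CK-MB level are joined by "and", and the sentence ends with the pointer to the Appendix.

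The Appendix has three parts:
- Part A is Q-wave infarction: the ECG criteria of part C plus "CK-MB elevation 5 × upper limit of normal".
- Part B is "Enzymatic/non-Q-wave infarction", with the same CK-MB criterion and nothing else.
- Part C lists the ECG criteria. Some are not Q waves, for example "New permanent LBBB and enzyme elevation", a posterior R-wave pattern and reversed R-wave progression.

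The Appendix gives no time window and no link to a procedure.

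The section on primary composite end points counts "nonfatal myocardial infarction, and refractory angina requiring revascularization across 5 years of follow-up". The section on secondary end points says that "cardiac death, myocardial infarction, and repeat revascularization procedures will be assessed in-hospital and at 1, 6, and 12 months and yearly thereafter". The Methods section sends nonfatal events to a blinded Clinical Events Committee, which is to adjudicate uniformly.

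**The concern.** A primary component needs one rule that covers the whole period over which it is counted. Here there are two rules, and they disagree on Q waves, on other ECG patterns and on timing. Neither contains a separate criterion for MI that is unrelated to a procedure. The choice between them decides which patients have a primary event. It is left open, so an adjudicator can follow the protocol and reach either answer for the same record. If Table 2 is followed literally, the component becomes a periprocedural Q-wave endpoint, although the protocol describes and schedules it as a 5-year endpoint.

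**Working it through.** **1. The two rules side by side.** The patients below are illustrative and nonfatal. "Late" means more than 14 days from any revascularization, for example an event found at the 24-month visit.

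| Event | Table 2 | Appendix |
|---|---|---|
| Day 3, new Q waves in 2 contiguous leads, CK-MB 6 × upper limit | MI | MI (A) |
| Day 3, no Q waves, CK-MB 6 × | not MI | MI (B) |
| Day 3, new permanent LBBB without Q waves, CK-MB 6 × | not MI | MI (A through C, or B) |
| Late, new Q waves, CK-MB 6 × | not MI | MI (A) |
| Late, no Q waves, CK-MB 6 × | not MI | MI (B) |
| Late, no ECG criterion, CK-MB below 5 × | not MI | not MI |

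The rules agree on the first and last rows and disagree on the four between. The last row shows what choosing the Appendix would leave open: a late infarction is still judged by the one 5-fold enzyme threshold or the ECG list.

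**2. Share of time covered by Table 2.** For a patient with the index operation only, the window is 14/1826 days = 0.77% of 5 years. This is a share of time, not of events. The protocol gives no timing of infarctions.

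**3. The protocol's own sample size.** Inputs from Methods: 95% event-free at 5 years on-pump, a decrease of not more than 10% off-pump, α 0.05, β 0.20, 153 per group. The formula for two proportions with pooled variance, two-sided, is

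n = [1.96·√(2p̄q̄) + 0.842·√(p₁q₁ + p₂q₂)]² / (p₁ − p₂)².

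- Relative reading (event rates 5% and 14.5%): [1.96·√0.17599 + 0.842·√0.17148]² / 0.095² gives 152 per group.
- Absolute reading (5% and 15%): the same formula gives 141. Freedman's log-rank formula gives 30 events, and 30/(0.05 + 0.15) = 150 per group.

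The stated 153 is therefore reproduced closely by two routes. It does not depend on how MI is defined, so it neither supports nor weakens the point.

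**4. Cost if events were lost equally in both arms.** The protocol does not state the MI share of primary events, so the loss fraction m is an assumption. Start from 5% and 15%, and multiply both by (1 − m). Power at n = 153 is

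Φ{[|p₁ − p₂|·√153 − 1.96·√(2p̄q̄)] / √(p₁q₁ + p₂q₂)}.

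- m = 0: (0.10·12.369 − 1.96·√0.18)/√0.175 = 0.969, so power is 83.4%.
- m = 20% (4% and 12%): (0.08·12.369 − 1.96·√0.1472)/√0.144 = 0.626, so power is 73.4%.

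| Loss m | Expected events, 153·(p₁ + p₂) | Power at 153 | n per group for 80% |
|---|---|---|---|
| 0% | 30.6 | 83.4% | 141 |
| 10% | 27.5 | 78.8% | 158 |
| 20% | 24.5 | 73.4% | 180 |
| 30% | 21.4 | 67.1% | 208 |
| 40% | 18.4 | 59.9% | 245 |

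**The case against.** The strongest reply is that Table 2 refers to the Appendix, whose title is the definition of MI, so the Appendix may be the operative text. Table 2 also mentions enzymes twice in one sentence, which suggests a garbled condensation of parts A and B. On that reading non-Q-wave MI counts, and so does later MI with CK-MB at 5 times the upper limit. This stands as a possibility. A reader might infer from Table 2 that late and non-Q-wave infarctions are in fact being lost. The protocol supports that only if Table 2 governs, and it does not say so. Equally, it does not say that the Appendix overrides an explicit Q-wave requirement in the table that Methods names as the source of the definitions.

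The second reply is partial capture, and it also stands. Fatal MI counts as cardiovascular death. A Q-wave MI within 14 days of a repeat revascularization still meets Table 2. Some patients with a late MI will enter through refractory angina requiring revascularization. Under Table 2 the loss is confined to nonfatal MI, and a patient drops out of the composite only if no other component occurs.

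The third reply is that a blinded committee adjudicates. Blinding limits differential classification between arms, but it does not tell the committee which rule to apply. Nor is this a matter of detail left to a fuller document: the article prints both definitions, and they conflict.

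**Conclusion.** The MI definition is wrong as written and needs correction before the primary analysis. That conclusion rests on the contradiction between Table 2 and the Appendix, and on the absence in both of a rule for spontaneous MI. It does not rest on a count of lost events.

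Three stronger readings are not supported:
- *The comparison is biased toward no difference.* If events drop out in similar proportion in both arms, power falls but the hazard ratio need not move. Bias would require a different treatment effect on the dropped events, and the protocol gives no figure for that.
- *Late MI is the harm that the protocol attributes to off-pump surgery.* The Introduction names patency, repeat revascularization and mortality. The Rationale names safety, early anastomotic failure and incomplete revascularization. Neither mentions late MI.
- *A fifth to a third of events would go.* Losing 3 to 5 events is 20% to 33% of 306 × 0.05 = 15.3 events, but only 10% to 16% of the 30.6 expected at 5% and 15%. The 3 to 5 is itself an assumption without a source in the protocol.

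The power figures above (83.4% falling to 73.4% at a 20% loss) are conditional on Table 2 governing, on 5% and 15% event rates, on a two-sided test and on equal proportional loss.

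**What to change.** Reconcile Table 2, the Appendix and the primary and secondary end point sections into one MI definition that states:

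1. which periprocedural rule governs, Table 2 (Q waves plus enzymes) or Appendix B (enzymes alone), and whether the ECG patterns in Appendix C other than Q waves qualify;
2. the window for that rule, and that it runs from any revascularization, if that is the intention;
3. a separate rule, with its own biomarker and ECG or symptom criteria, for MI outside that window through 5 years.

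Methods reports that an interim analysis of events by arm has been performed. The definition should therefore be chosen by people who are blind to treatment arm and to interim results, and the amendment should record this. The blinded events committee should then re-read every event already adjudicated under the unified text. The periprocedural rule that was not chosen should be reported as a sensitivity analysis of the primary comparison.

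The cost is an amendment and the re-reading of existing records. Events that were never referred because they did not meet the rule then in use would have to be sought in the visit records. The sample size does not need to change on this ground.
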